#### Sample Size Calculations

Anticipating an attrition rate of 20% throughout the study, n = 125 participants are required to achieve a final sample size of n = 100. Sample size analysis indicated that 50 subjects per group (intervention and control) or a total of 100 are required to complete the study in order to detect an absolute intervention effect with 80% power and type I error of 5% (two-tailed). Sample size was calculated based on an overall difference between participants in the intervention and control groups in the primary outcome measure of depression scores at 6 months, where a sample size of n = 100 was sufficient to detect a difference in mean CDS scores of 6.8, assuming a between-patient SD of 12 [29]. Assuming persistence of effect to 12 months and a conservative correlation of 0.30 between baseline, 6 months and 12 months CDS scores, a pooled analysis at 6 and 12 months will have 80% power to detect a difference of 5.1 units (a change score of 5 on the CDS is considered clinically meaningful).

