### Study Integrity

The study design is guided by the CONSORT statement [33] and randomisation to study group occurs following the completion of Time 1 data collection. Project staff who are collecting data are blinded to participants' group allocation. Participants are asked not to reveal the group to which they have been randomised when completing data assessments. Stratified randomisation occurs using a separate block randomisation list that has been generated for each study group or strata. Randomisation is integrated into the web-based database and automatically generated following the conclusion of baseline assessment. The process is concealed from investigators. The schedule is stratified by severity of depression assessed by the CIDI (i.e. those meeting current diagnosis for depression versus those who do not). The intervention protocol is detailed in a manual. In addition to internal peer review, all intervention calls are audio-taped with a proportion reviewed by a senior clinical psychiatric consultant, using a standardised inventory in order to ensure clinicians' adherence to the delivery of the intervention protocol and treatment integrity. To assess the quality of the delivery of the intervention, a separate inventory based on the Cognitive Therapy Scale [34] has been developed for the MoodCare intervention. All data analyses are conducted on the basis of intention to treat.

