### Data Analyses

Baseline characteristics will be compared across intervention arms using summary statistics. Principal analyses will involve comparison of CDS and HRQOL outcomes at each time point between intervention arms using the baseline of the outcome as a covariate where relevant. Pooled analyses across all time points will employ linear mixed models. This will assess comparative rates of change over time, variability between rates of individuals, and allows for incomplete data due to a process of missingness where systematic dependence is upon observed covariates or outcomes, the so called "missing at random" assumption. Results will be expressed as estimated mean changes in CDS depression measures and HRQOL, as an overall mean excess intervention over usual care effect, all with corresponding 95% confidence intervals.

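### The CIDI stratum used for randomisation is not named in the analysis model, and adjustment for the baseline outcome is left conditional (minor; a free improvement)

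*Protocol article*

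**What the plan says.** Under Study Integrity, the protocol article states: "The schedule is stratified by severity of depression assessed by the CIDI". The two levels are a current depression diagnosis or none. On the method it says: "Stratified randomisation occurs using a separate block randomisation list that has been generated for each study group or strata". Randomisation follows completion of the Time 1 assessment, so each participant's stratum is known before allocation.

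Under Data Analyses, the principal comparisons of CDS and HRQOL between arms at each time point are made "using the baseline of the outcome as a covariate where relevant". The next sentence reads: "Pooled analyses across all time points will employ linear mixed models". No fixed effects are listed for those models, and the CIDI stratum does not appear in the section.

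Under Sample Size Calculations, the 6-month comparison is sized to "detect a difference in mean CDS scores of 6.8, assuming a between-patient SD of 12", "with 80% power and type I error of 5% (two-tailed"). The same paragraph gives a pooled 6- and 12-month detectable difference of 5.1 units, with a correlation of 0.30 between baseline, 6-month and 12-month CDS.

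**The concern.** Blocking within strata balances the arms on the stratification factor, so variation between strata largely drops out of the treatment comparison. A model without the factor still counts that variation as residual error. The reported standard error then exceeds the true one: intervals are too wide, the test rejects less often than 5% under the null, and some power is given away. All of this depends on the factor predicting the outcome after the baseline score is in the model.

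The qualifier on the baseline covariate is a second, separate matter. Table 1 schedules both CDS and SF-12 at Time 1, so a baseline value is planned for both primary outcomes and the condition has no evident purpose. Read literally, it leaves a choice open in the principal analysis, although one of the article's own power figures needs the adjustment.

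**Working it through.** **1. The plan's own 6-month figure.** Inputs from Sample Size Calculations: difference 6.8, SD 12, 50 completers per group, two-sided 5%, 80% power.

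- Unadjusted standard error: 12 × √(2/50) = 2.40.
- Detectable difference: (1.96 + 0.84) × 2.40 = 6.72, against 6.8 stated.
- Power for 6.8: Φ(6.8/2.40 − 1.96) = Φ(0.87) = 80.9% (80.1% with the t distribution).
- Enrolment: 100/0.80 = 125, as stated.

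The figure reproduces. It uses the full SD of 12, so it relies on no covariate.

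**2. The pooled figure.** For the mean of two follow-ups with correlation r = 0.30, the variance factor is (1 + r)/2 = 0.65 without baseline adjustment and (1 + r)/2 − r² = 0.65 − 0.09 = 0.56 with it.

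| Analysis | Starting from 6.8 | Starting from 6.72 |
|---|---|---|
| Baseline adjusted, × √0.56 | 5.09 | 5.03 |
| Not adjusted, × √0.65 | 5.48 | 5.42 |

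The stated 5.1 matches only the adjusted row. Power for 5.1 units:

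- Adjusted: standard error 2.40 × √0.56 = 1.796; Φ(5.1/1.796 − 1.96) = 81%.
- Not adjusted: standard error 2.40 × √0.65 = 1.935; Φ(5.1/1.935 − 1.96) = 75%.

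**3. Leaving out the stratum.** Let p be the CIDI-positive share and d the gap in outcome between strata that remains after baseline adjustment, in within-stratum SDs. Neither is in the article. Assumed ranges: p = 0.3 to 0.5, d = 0.3 to 0.8.

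- Standard error inflation: f = √(1 + p(1 − p)d²).
- True type I error: 2 × (1 − Φ(1.96f)).
- Extra sample needed to recover 80% power: ((1.96f + 0.84)/(1.96 + 0.84))² − 1. Only the critical value is multiplied by f, because blocking leaves the true variance of the estimate uninflated.

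| p, d | p(1 − p)d² | f | Type I error | Sample equivalent |
|---|---|---|---|---|
| 0.3, 0.3 | 0.019 | 1.009 | 4.8% | about 1.3% |
| 0.5, 0.8 | 0.160 | 1.077 | 3.5% | about 11% |

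With d = 0, f = 1 and nothing is lost.

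**4. Power with and without the stratum.** Baseline CDS in the model at r = 0.30 gives a residual SD of 12 × √(1 − 0.09) = 11.45. With 50 per group and a difference of 6.8, let q be the share of residual variance that the stratum explains (assumed 0 to 0.15).

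| q | Power, stratum omitted | Power, stratum included |
|---|---|---|
| 0 | 84.4% | 84.4% |
| 0.02 | 84.6% | 85.1% |
| 0.05 | 85.0% | 86.2% |
| 0.10 | 85.7% | 87.9% |
| 0.15 | 86.3% | 89.7% |

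The cost of omission is 0 to about 3 points, and power stays above 80% throughout.

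**5. Simulation check.** Blocked allocation within strata was simulated with 6,000 trials per setting, assuming 40% CIDI-positive and a correlation of 0.5 between stratum and baseline CDS. Direct stratum effects of 0, 3, 5 and 8 CDS points gave type I error of 4.9%, 4.7%, 4.5% and 4.0% with the stratum omitted. Power was 83.4%, 86.1%, 86.8% and 89.2% without the stratum, and 83.4%, 86.3%, 87.6% and 91.6% with it. Direction and size agree with the formulas.

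**The case against.** The strongest reply is that a journal article condenses the plan, and that a full covariate list, stratification factors included, is commonly left to the full protocol or SAP, which are not shown. This stands in part. A reader might infer that the analysis adjusts only for baseline, but the text names one covariate without ruling out others, and for the mixed models it names none. What remains is that the article does state a covariate rule, and that rule omits the one factor used to stratify.

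A second reply is that baseline CDS may already carry most of what the diagnosis adds. The article credits the CDS with 97% sensitivity and 85% specificity for major depression, so for the CDS outcome the residual effect may be small. This also stands in part. The assumed correlation of 0.30 means that baseline explains only about 9% of outcome variance, and nothing in the article shows that baseline SF-12 captures the diagnosis.

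Two stronger readings are tempting and not supported:

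- A reader might infer that standard errors are definitely too large and that planned power is lost. The first depends on a residual effect that the article does not quantify. The second fails because the 80% was computed with no covariates.
- A reader might turn the variance term directly into a sample loss of 2-16%. That treats the true variance of the estimate as inflated, when only the reported standard error is; the figure is about 1-11%.

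On the baseline qualifier, it can fairly be said that a mixed model over all time points may treat baseline as a response rather than a covariate. That is legitimate, and the fix allows for it.

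**Conclusion.** The point holds as a minor one. The covariate rule omits the stratification factor. If followed as written, it gives conservative intervals whenever CIDI diagnosis predicts CDS or SF-12 beyond the baseline score. Under the assumed 30-50% CIDI-positive and residual gap of 0.3-0.8 SD, standard errors are about 1-8% too large, true type I error falls to between 4.8% and 3.5%, and the loss equals about 1-11% of the sample. If there is no residual effect, the loss is zero. Type I error stays at or below 5%, and the planned 80% power for 6.8 points at 50 completers per group does not depend on the stratum.

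The baseline part needs no outside assumption. The article's 5.1-unit figure reproduces only with baseline adjustment, and power for that difference drops from about 81% to 75% without it. The analysis section should therefore not make that adjustment conditional.

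**What to change.** In Data Analyses, or in the SAP if it does not already say so:

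- Include the CIDI randomisation stratum as a fixed effect in the principal comparisons and in the mixed models.
- Remove the qualifier on baseline adjustment for CDS and SF-12. Always account for the baseline value, either as a covariate or as a baseline response in a mixed model that constrains the arms to a common baseline mean.

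The cost is a sentence or two of text and one degree of freedom for the stratum. Both variables are collected before randomisation, so no new data are needed and the sample size does not change.

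Label: free improvement, minor severity.

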## Discussion

Depression often remains unrecognised and untreated in cardiac patients, despite increasing the risk of poor patient outcomes such as reduced HRQOL and increased mortality (including suicide). For the first time, this study will evaluate the feasibility, efficacy and cost-effectiveness of a state-of-the-art, tele-based depression management and CHD secondary prevention program for depressed ACS patients. If feasible and successful in promoting depression and HRQOL benefits, the intervention could provide an alternative for those who cannot tolerate or would prefer a non-pharmacological alternative to depression treatment. Further, this contemporary tele-health approach to management may help overcome some of the barriers to participation that are associated with face to face rehabilitation programs, including distance, cost and time. The intervention could be translated into clinical practice through community-based telephone helplines widely used in Australia and internationally or through acute clinical care settings.

## List of abbreviations

CHD: Coronary Heart Disease; MI: Myocardial Infarction; MDD: Major Depressive Disorder; HRQOL: Health Related Quality of Life; ACS: Acute Coronary Syndrome; CBT: Cognitive Behaviour Therapy; UC: Usual Care; CDS: Cardiac Depression Scale; SF-12: Short Form-12; STEMI: ST elevation Myocardial Infarction; Non STEMI: Non-ST elevation Myocardial Infarction; PHQ9: Patient Health Questionnaire; CIDI: Composite International Diagnostic Interview; CONSORT: Consolidated Standards of Reporting Trials; HbA1c: Haemoglobin A1C; BMI: Body Mass Index; GP: General Practitioner; CATI: Computer Assisted Telephone Interview; CEA: Cost-effectiveness analysis; HCU: Health Care Utilisation; PBS: Pharmaceutical Benefits Scheme; APACHE III: Acute Physiology And Chronic Health Evaluation III; QALYs: Quality-adjusted life years
